**Project summary**

**Rationale**

To date, it is still debated how much inflammation per se contributes to pain in osteoarthritis. A variety of studies have investigated various aspects such as synovitis but still, no clear associations to pain have been found. Many studies have attempted to modulate the effect of the inflammatory mediators on the pain receptors by e.g., interacting with the arachidonic acid pathways. As such compounds have both peripheral and central effects it is difficult to use such compounds as specific modulators of specific local inflammatory processes. So far, no compounds have been used to modulate selectively the local organelles involved in the inflammatory processes of joint pain.

**Objectives**

The purpose of this study is to investigate if specific effects can be obtained by modulating selectively macrophages and mast cells in the osteoarthritic knee joint as assessed by mechanistic pain assessment tools (quantitative sensory testing), blood and synovial fluid analysis, and clinical pain ratings in patients with painful knee osteoarthritis.

The aim of this study is to use gold particles as a model compound to modulate specifically and selectively the function of macrophages and mast cells and investigate how this modulates pain and pain sensitization, clinical outcome, and proteomic markers in synovial fluid and serum.

**Methods**

Approximately 72000, 20-40 my-meter diameter, sterilized gold particles (=20 mg) will be provided in vials (The Berlock® Gold Implants). 5-10 ml of synovial fluid is aspirated (20G needle) from the affected OA knee. The vial of gold microparticles is mixed with 2 ml synovial fluid**,** and the mix of gold and synovial fluid is injected intra-articularly into the patient’s knee. The remaining synovial fluid and blood samples are stored for future analysis.

We will include 30 patients in group I for evaluation of the modulation of macrophages and mast cells. Quantitative sensory testing, patient-reported questionnaires, clinical examination, and blood and synovial samples will be collected before and 8 weeks after treatment. At the 2-year follow-up, patient-reported questionnaires and additional treatments will be collected.

Patients who have not fulfilled the criteria for evaluation of the modulation of macrophages and mast cells will be included in group II and will be treated using gold microparticles and hyaluronic acid and followed using patient-reported questionnaires. This group will be followed for evaluation of the generalized effect on pain and function. This group will be followed before, 8 weeks after, and at 2 years using patient-reported questionnaires, and additional treatments will be collected.

**Expected outcome**

For the included 30 patients we expect a difference of 0.5 SD in the primary outcome, the patient-reported pain, and the function questionnaire WOMAC. For the total sample of included and excluded patients, we expect more than 70% to report a benefit of treatment on a global outcome measure.

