***Clinical pain and function assessment***

WOMAC Pain, function and stiffness score

The Western Ontario and McMaster Universities Arthritis Index WOMAC [6] is a subject-rated instrument that measures Osteoarthritis (OA) symptoms. The questionnaire contains 5 pain questions, 2 stiffness questions, and 17 physical function questions (24 questions total). Each question utilizes a 5-point scale, from 0 (none) to 4 (extreme). The WOMAC score will be used before treatmen and 8 weeks and 2 years after.

Weekly Pain Diary

Subjects rated their pain intensity on a VAS scale every day at home. On the VAS scale ‘‘0” indicates ‘‘no pain”, and ‘‘10” indicates ‘‘maximal pain”. Subjects rated the pain severity for Average Pain Score (APS) for the last 24 hours, worst pain for the last 24 hours, and pain severity at night. The weekly pain diary will be used for 8 weeks after treatment.

Global Rating of Change Scale

Using the Global Rating of Change Scale, we asked the question, “Concerning your knee, how will you describe yourself compared to immediately before the injection of gold into your knee” and evaluated the answer on an 11-point scale from very much worse (-5) to complete recovered (5) with a score of “0” indicating no changes. The global rating scale will be used 8 weeks and 2 years after treatment.

Pain Detect questionnaire (PDQ)

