**Statistical analysis**

This present exploratory study will investigate whether gold ions have a clinical role in treating KOA. Based on preclinical evidence, we estimated medium effect size (Cohen’s d = 0.5), and with a power of 80% and a significant level at 0.05, a sample size calculation estimated a total sample of 27 subjects will be needed in group 1. A total of 30 subjects will be included to account for possible drop-out.

The clinical outcome measures analysis will be performed using the Stata software, version 16.0 (StataCorp.) ANOVA will be used for the analysis of repeated measures of pain, the pain diary, and QST parameters. Wilcoxon test will be used for all other measurements.

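### The primary outcome is not tied to one WOMAC score or one visit, although group 1 is sized for a single comparison at 0.05

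*Protocol*

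**What the plan says.** The only statement of the primary outcome is in the project summary, under Expected outcome, for the 30 patients of group 1: "we expect a difference of 0.5 SD in the primary outcome, the patient-reported pain, and the function questionnaire WOMAC". No visit is given there.

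The section Clinical pain and function assessment describes the instrument: "The questionnaire contains 5 pain questions, 2 stiffness questions, and 17 physical function questions (24 questions total". No subscale or total is singled out. On timing it says: "The WOMAC score will be used before treatmen and 8 weeks and 2 years after". The same section adds a second patient-reported pain measure, a VAS diary of average, worst and night pain: "The weekly pain diary will be used for 8 weeks after treatment".

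The Statistical analysis section sizes group 1 as follows: "we estimated medium effect size (Cohen’s d = 0.5", "with a power of 80% and a significant level at 0.05", and "a sample size calculation estimated a total sample of 27 subjects will be needed in group 1", raised to 30 for drop-out. It names no outcome, visit, test or sidedness for this calculation. On tests it says: "ANOVA will be used for the analysis of repeated measures of pain, the pain diary, and QST parameters". Everything else goes to a Wilcoxon test. The section calls the study exploratory.

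**The concern.** A sample size of 27 for one standardised difference at 0.05 presumes one score, compared with baseline at one visit. The protocol never identifies that comparison. WOMAC pain and WOMAC function are both candidates, each at 8 weeks and at 2 years. The diary is also patient-reported pain, so even the instrument can be questioned.

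The test is not settled either. WOMAC pain is a repeated measure of pain, so on the literal reading it goes to ANOVA, while function goes to Wilcoxon. The primary instrument is then split between two methods. A WOMAC total mixes pain with other items and has no clear place, and if pain in that sentence means only VAS ratings, WOMAC pain moves to Wilcoxon.

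Group 1 has no control arm, so the before-after test on the primary outcome is its main inferential result. If the deciding score and visit can be chosen after the data are seen, the 0.05 used in the sample size no longer describes the chance of a false positive claim.

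**Working it through.** **1. The plan's own figure.** Inputs from Statistical analysis: d = 0.5, power 80%, level 0.05, n = 27. With no control group, the natural model is a paired t-test on one change, with d taken as mean change divided by the SD of change (the protocol does not say which SD is meant).

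The test statistic follows a noncentral t distribution with n − 1 degrees of freedom and noncentrality d × √n. At n = 27 this is 0.5 × √27 = 2.60; at n = 30 it is 0.5 × √30 = 2.74.

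| Test at 0.05 | Smallest n for 80% | Power at 27 | Power at 30 |
|---|---|---|---|
| One-sided paired t | 27 | 81.2% | 84.8% |
| Two-sided paired t | 34 | 70.6% | 75.4% |

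The figure of 27 is reproduced exactly as one comparison tested one-sided. The same inputs tested two-sided need 34.

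**2. Candidate primary results.** Two scores (pain, function) at two post-treatment visits (8 weeks, 2 years) give 2 × 2 = 4 comparisons with baseline. Stiffness is not mentioned where the primary outcome is named, so it is not counted.

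**3. Chance of at least one false positive, each test at 0.05, if any one counts as success.** Under independence it is 1 − 0.95^k:

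- k = 2: 1 − 0.95² = 9.75%
- k = 4: 1 − 0.95⁴ = 18.5%

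These results would be positively correlated, which lowers the figures. The protocol gives no correlations, so I assume 0.6-0.8 between scores and 0.4-0.6 between visits. Simulating correlated normal test statistics (400,000 draws, two-sided 0.05) gives:

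| Family | At least one false positive |
|---|---|
| Pain and function, one visit | 7.7-8.7% |
| Pain and function, both visits | 13.4-16.0% |

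With a wider range (scores 0.3-0.8, visits 0.5-0.8), and allowing one-sided or two-sided tests, the figures are about 7-10% and 11-17%.

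**4. Contribution of the test choice.** Applying both a t-type test and a Wilcoxon test to the same single change, and counting either, gives 5.8% at n = 27 and 5.4% at n = 30 in simulation. Nearly all of the inflation therefore comes from the open score and visit.

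**5. Does 27 conflict with ANOVA?** For a three-visit repeated-measures ANOVA with f = 0.25 (d/2) and an assumed correlation of 0.5 between visits, power is 79.6% at 27 and 84.1% at 30. So 27 is not shown to be wrong for that test; the protocol simply does not say which test it was calculated for.

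**The case against.** **The 0.05 level is not shown to fail.** A reader might infer that the trial's 5% level is already broken. The documents do not support that. Inflation needs a rule that any one significant result is success, and no such rule is written. If one score and visit were fixed, or if all had to be significant, there would be no inflation. The study calls itself exploratory, and multiplicity rules are commonly left to an analysis plan, which may exist. This stands, and it makes the percentages conditional. It does not remove the gap: which score and visit are primary belongs in the protocol, because the sample size depends on it.

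**WOMAC pain does not fall under both tests.** A reader might infer that it does. Wilcoxon is reserved for whatever ANOVA does not cover, so the two lists exclude each other. What remains is a split instrument, and doubt about a WOMAC total and about the meaning of pain in that sentence.

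**The wording may describe one instrument.** The sentence under Expected outcome can be read as a single pain-and-function questionnaire, not two outcomes. That is fair. On that reading the score and the visit are still open.

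**Three scores at two visits.** A larger family that includes stiffness might be tempting, but stiffness is not part of the stated primary outcome.

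**The sample size may fit an ANOVA.** As step 5 shows, a three-visit ANOVA comes close to 80% power at 27 under an assumed correlation. A claim that 27 fits none of the planned tests is therefore not supported.

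**Conclusion.** The point holds as an under-specified primary outcome. The protocol fixes neither the WOMAC score nor the visit, while the sample size is a single-comparison calculation at 0.05 with no outcome, test or sidedness attached. The primary instrument is split between ANOVA and Wilcoxon on the literal reading.

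The size is conditional. If any one result counts as success, the false-positive chance is about 8-9% for pain and function at one visit and 13-16% at both, under the assumed correlations and two-sided tests. The choice of test alone adds little. The claim that 27 corresponds to a one-sided test assumes a paired t-test with d on the SD of change. The change is worth making, and the exploratory label does not make it unnecessary, because the protocol itself names a primary outcome, states a hypothesis and powers for it.

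**What to change.** In the protocol, name one primary outcome for group 1 by score, visit, test and sidedness. One workable choice is change in WOMAC pain from baseline to 8 weeks, the visit at which QST and the blood and synovial samples are also taken. Make WOMAC function and the 2-year scores secondary, reported with 95% confidence intervals. State which test applies to each WOMAC score, and to a total if one is used.

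Restate the sample size sentence for the chosen test. If it is a one-sided 0.05 paired t-test, say so; 27 then stands with 81% power. If it is two-sided, state the power as about 71% at 27 and 75% at 30.

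The cost is protocol wording; no new data are needed. Function and the 2-year results lose primary status, and the stated power is less favourable if the test is two-sided.

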**Rationale & Background information**

Osteoarthritis (OA) of the knee and hip is the most common musculoskeletal joint disease worldwide. Although a major symptom of OA is chronic joint pain, which has a significant effect on patients’ quality of life, the pain mechanisms remain largely unknown.

Recently, clinical studies have suggested the existence of a neuropathic component in OA pain [5]. Accumulating evidence has been indicating that painful OA patients show peripheral and central sensitization [3,16]. Quantitative sensory testing (QST) is a relevant way to assess peripheral and central sensitization in joint pain [9]. Several of the studies have administered mechanical stimuli, and the most often used modality has been pressure. A recent review concluded that people with OA have lower Pressure Pain Thresholds (PPT), facilitated temporal summation, and impaired conditioned (CPM) compared with healthy controls [5]. Also, recent evidence has linked QST profiles to the development of chronic pain [29,38], which emphasizes the importance of studying the central nervous system.

Inflammation markers have been correlated with pain intensity [35], and systemic inflammation can lead to sensitization of peripheral nociceptors [1]. Recently it was reported that higher preoperative levels of TNF-α, MMP-13, and IL-6 in synovial fluid may indicate a smaller improvement in pain 2 years after TKR [15].

Injectable solutions of gold-thio-compounds have been used to treat rheumatoid arthritis for nearly 100 years [13,21]. Several studies suggest that gold ions reduce pain, joint swelling, and inflammation, and increase joint motility [24,31,33]. Gold salt therapy (auranofin; RidauraR) has been vetted by the FDA and approved (May 1985) and recommended by the American College of Rheumatology as a Disease Modifying Anti Rheumatic Drug - DMARD (https://www.rheumatology.org).

Gold salts, whether injected or given orally, are effective [33,37] in reducing joint pain. Studies report patients going into total remission [28] and others report a 30% reduction in symptoms [20,27]. In addition, Clark et al., 1997 [8] concluded in a Cochrane meta-analysis that systemic treatment with gold was highly effective compared to placebo.

The use of gold salt given systemically has been criticized since when gold compounds are made to circulate systemically via the circulatory system after oral or parenteral administration, the gold ions reach essentially all tissues and organs. In some patients, organs that are not involved in the arthritic disease, such as the kidneys, liver, and skin are adversely affected by gold. About 30% of patients develop such remote organ “side effects” and discontinue gold treatment [20]. In addition, newer drugs have been developed with efficacy almost equal to gold ions in many patients, and less toxic.

To overcome the toxicity, a method that captures the efficacy of the gold ions but eliminates the remote side effects have been developed[10,23]. Briefly, the method isolates the gold ions within the affected joints by injecting solid gold metal directly into the diseased joint, whereby a very slow dissolution and local diffusion deliver the therapeutic gold ions to affected areas within the joint. In this therapy, 99.99% pure gold implants are injected into the body.

Individual single beads are implanted with a 16-gauge needle based on an X-ray picture in deeply anesthetized animals close to the capsule of the affected joint(s) (videos www.goldtreat.com). Over *3*000 dogs and more than 100 horses have had this treatment for osteoarthritis at 50+ veterinary clinics and hospitals throughout Europe, (www.goldtreat.com). Success rates of 50 – 70% are quoted (www.goldtreat.com), and a double-blind, placebo-controlled study on dogs showed improvement in over 80% of the dogs, which continues for 18 months [18] as the gold particles remain in the joint[26].

The systemic concentration of released gold ions is low but clinically effective and because the gold ions do not spread in the organism, but instead stay local, the technique is safe [12]. The trials to date indicate that only one local application is needed to obtain lifelong clinical effects [12].

To date, it is still debated how much inflammation per se contributes to pain in osteoarthritis. A variety of studies have investigated various aspects such as synovitis but still, no clear associations to pain have been found[30]. Many studies have attempted to modulate the effect of the inflammatory mediators on the pain receptors by e.g., interacting with the arachidonic acid pathways[4]. As such compounds have both peripheral and central effects it is difficult to use such compounds as a specific modulator of specific local inflammatory processes. So far, no compounds have been used to modulate selectively the local organelles involved in the inflammatory processes of joint pain.

Gold particles seem as the only known method to obtain such a local effect on one specific element involved in the inflammatory process – the macrophages and the mast cells.

If a foreign object gets embedded in the body, macrophages will attack the object and digest it. If the foreign object has a diameter bigger than 20 microns, the macrophage cannot engulf it. Instead, the macrophages create a membrane on the surface of the foreign body and start a chemical attack in order to dissolve it. If the foreign body consists of gold the macrophages will cause the release of gold ions from the foreign body.

Gold ions, taken up by the macrophages, cause them to malfunction[10,11,23]. As the macrophage is a ‘conductor’ of the inflammatory process it causes a drastic restraint of the inflammation and finally brings it to a stop[22,25]. The released gold ions will be taken up by the macrophages themselves, but also diffuse out into the surrounding tissue where they are taken up by other cells as well e.g. mast cells and other connective tissue cells[7,32]. When the gold ions accumulate in the secretory granules of mast cells it blocks histamine release and thereby decreasing local edema, and additionally suppressing pain.

The amount of bio-released gold ions is related to the intensity of inflammation. Only a few gold ions are released in immunological nonreactive tissue. This means that if a local inflammation that has been treated with gold implants, the increase in macrophages will cause an immediate inhibition of the inflammation.

The combined effect of gold ions on macrophages and mast cells is together believed to cause a significant reduction in pain following treatment with metallic gold particles. If this principle can be validated, it may provide important information for the development of new and better treatments for e.g., joint pain.

Recently, Seifert et al.[34] called for studies providing new insights into the mode of action of gold ions and suggest investigating the effects on key mechanisms involved in arthritis or other inflammatory conditions.

The aim of this study is to use gold particles as a model compound to modulate specifically and selectively the function of macrophages and mast cells and investigate how this modulates pain and pain sensitization in the osteoarthritic knee assessed by mechanistic pain assessment technologies (QST).

**Study goals and objectives**

The purpose of this study is to investigate if specific effects can be obtained by modulating selectively macrophages and mast cells in the osteoarthritic knee joint as assessed by mechanistic pain assessment tools (quantitative sensory testing), blood and synovial fluid analysis, and clinical pain ratings in patients with painful knee osteoarthritis.

Hypothesis: Modulating macrophages and mast cells by gold microparticles injected into the osteoarthritic knee joint will modulate inflammation specifically, inhibit pain sensitisation and provide pain relief to patients with knee OA.

The aim of this study is to use gold particles as a model compound to modulate specifically and selectively the function of macrophages and mast cells and investigate how this modulates pain and pain sensitization, clinical outcome, and proteomic markers in synovial fluid and serum.

**Study design**

**Patients**

***Group 1***

For this part of the study 30 patients with single knee OA will be included using a narrow set of inclusion and exclusion criteria for evaluation of the modulation of macrophages and mast cells.

The following inclusion and exclusion criteria will be used.

Patients with radiographically confirmed KOA (Kellgren-Lawrence grade ≥ 2), pain for more than three months, and maximal pain intensity VAS (Visual Analogue Scale, 0-10) ≥ 5 during the last week, and with knee joint effusion on MRI that can be aspirated. Eligible patients were enrolled at the specialized, public outpatient clinic at Aalborg University Hospital, Denmark. The exclusion criteria were: 1) active adjuvant treatment for any malignancy, 2) active infection and antibiotic treatment, 3) active treatment with steroids, biological or other anti-rheumatic medication, 4) chronic pain and other than knee joint pain, 5) inability to comply with the protocol and, 6) inadequacy in written and spoken national language.

***Group 2***

During the inclusion period for group 1, we will include a group of patients with minor degree of knee OA, chronic pain, and other pain than knee joint pain (multisite pain) for evaluation of the generalized effect on pain and function.

The following inclusion and exclusion criteria will be used.

Patients with radiographically confirmed KOA (Kellgren-Lawrence grade ≥ 1), pain for more than three months, and maximal pain intensity VAS (Visual Analogue Scale, 0-10) ≥ 5 during the last week. Eligible patients were enrolled at the specialized, public outpatient clinic at Aalborg University Hospital, Denmark. The exclusion criteria were 1) active adjuvant treatment for any malignancy, 2) active infection and antibiotic treatment, 3) active treatment with steroids or biological medication, 4) inability to comply with the protocol and 5) inadequacy in written and spoken national language.

The expected duration of the study is 4-5 years with an inclusion period of two years and a follow-up time of two years.

**Methodology**

Approximately 72000, 20-40 my-meter diameter, sterilized gold particles (20 mg, sterile 99,99% pure gold microparticles) will be provided in vials (The Berlock® Gold Implants) for both groups.

***Group 1***

5-10 ml of synovial fluid is aspirated (20G needle) from the affected OA knee. The vial of gold microparticles is mixed with 2 ml synovial fluid**,** and the mix of gold and synovial fluid is injected intra-articularly into the patient’s knee. The remaining synovial fluid and additional blood samples are collected and stored for future analysis.

